**Conclusions:**

We anticipate that the intervention group will show significant changes in nutrition knowledge, attitudes, and practices; satisfaction with care; and overall diabetes management. We also expect to see urban-rural differences across the groups. The uniqueness of our nutrient data capture process is demonstrated by its cultural and contextually relevant features—diet capture in both English and Hindi, diet conversion into caloric components, sustained diet data collection and participant adherence through telephone-linked care, and auto-generated reminders.

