### Study Groups

The study participants were randomly assigned into the following two groups: the intervention group (telephone-linked dietary decision support system) and the control group (paper-based diet record; Figure 1). The randomization was conducted following the assessment of participants’ eligibility for inclusion in the study. Study participants in the intervention group (group 1) recorded their daily dietary intake by using a telephone-linked, personalized, human-centered dietary decision support system and received personalized feedback and diet education via SMS text messaging. The personalized, human-centered dietary decision support system is a telephone-linked decision support system designed to provide tailored dietary education to patients with diabetes. The study participants were able to access the personalized, human-centered dietary decision support system through their computers, cell phones, or a telephone-linked service, depending on the technology platform available to them. The telephone-linked service enabled the participants (including those who did not have a technology platform to access the personalized, human-centered dietary decision support system) to receive phone calls from our research team in order to record their daily dietary intake. The personalized, human-centered dietary decision support system also generated automatic alerts that served as reminders to the participants who had not reported their daily diet intake. Study participants in the control group were provided with a paper-based diet record for documenting their daily dietary intake. Both the intervention group and control group were provided with a diabetes educational booklet at baseline. However, the study participants in the control group were also provided with a booklet to document their diet log on a daily basis. Follow-up visits were conducted at 3 and 6 months from the baseline in both groups. Baseline data were gathered on sociodemographics; health literacy; physical activity; anthropometric measurements; blood sugar testing; and diabetes knowledge, attitudes, and practices (KAPs). Follow-up data were gathered on anthropometric measurements, diabetes KAPs, blood sugar testing, and satisfaction with medical care.

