#### Satisfaction With Medical Care

Satisfaction with medical care will be measured by using the Client Satisfaction Questionnaire-8 (CSQ-8). The CSQ-8 is an 8-item questionnaire in which items are rated by using a 4-point Likert scale [21].

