### Statistical Analysis

Baseline characteristics will be summarized and stratified by intervention group. The primary outcomes—adherence to dietary guidelines, KAPs, and patient satisfaction with medical care—will be compared between groups by using a log-rank test. A Cox proportional hazards regression model will be used to adjust for confounders that differ significantly between the two groups at the .20 level of significance. A generalized linear mixed model using a binomial distribution and logit link function will be used to examine the binary secondary objective—subjects’ satisfaction with medical care. The group types (ie, the intervention and control groups) will be used as a fixed effect, and subject data will be used as random effects. This will be done by using a variance components covariance structure. To adjust for confounders that differ significantly between the two groups at the .20 level of significance, covariates will be added to the model, and a linear regression model will be used.

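### Satisfaction with medical care is given two ranks, primary and secondary, and time-to-event, binary and linear analyses that cannot all fit one Likert-scale score

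*Protocol article*

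**What the plan says.** All of the conflicting statements stand in one paragraph, the Statistical Analysis section of the protocol article.

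- The primary outcomes are given as "adherence to dietary guidelines, KAPs, and patient satisfaction with medical care", and these "will be compared between groups by using a log-rank test".
- For adjustment of these outcomes, "A Cox proportional hazards regression model will be used to adjust for confounders that differ significantly between the two groups".
- Satisfaction then returns with a different rank and form: "A generalized linear mixed model using a binomial distribution and logit link function will be used to examine the binary secondary objective". Group is the fixed effect and subject the random effect.
- The paragraph closes on confounder adjustment: "covariates will be added to the model, and a linear regression model will be used".

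The section Satisfaction With Medical Care describes the measure: "The CSQ-8 is an 8-item questionnaire in which items are rated by using a 4-point Likert scale". The Outcomes section presents dietary KAPs as the study outcomes and mentions satisfaction as an addition. The Sample Size Justification rests on knowledge, attitude and behavior and does not mention satisfaction.

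On timing, Study Groups places satisfaction among the follow-up measures only: "Follow-up data were gathered on anthropometric measurements, diabetes KAPs, blood sugar testing, and satisfaction with medical care". The list of baseline measures in that section does not include it.

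**The concern.** A single outcome cannot be both primary and secondary, and it cannot be a time to an event, a binary response and a continuous score in the same confirmatory analysis. A reader of the results could not tell whether a favourable satisfaction finding was a primary result, which form of the score it used, or which of four named methods was meant to count. Rank, scale and model would all remain open to choice once the data are seen.

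The choice of form also affects precision. If the binary version were used, differences between scores on the same side of the cut would be discarded. The abstract's conclusions add a smaller difficulty: "We anticipate that the intervention group will show significant changes in nutrition knowledge, attitudes, and practices; satisfaction with care". With no baseline value, a change in satisfaction cannot be estimated; only a difference between groups at follow-up can.

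**Working it through.** **1. The statements side by side**

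| Statement in Statistical Analysis | Rank implied | Data type implied | Fit with the CSQ-8 as described |
|---|---|---|---|
| Log-rank test | Primary | Time to event | No event or time origin defined |
| Cox model | Primary | Time to event | Same |
| Binomial-logit mixed model | Secondary | Binary | Eight 4-point items are not binary without a cut |
| Linear regression for adjustment | Unclear | Continuous | Fits a total score, but is not the adjusted form of a logit model |

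No other section settles the rank or the form.

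**2. The plan's own sample-size figure**

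Inputs from Sample Size Justification: difference 0.2, SD 0.7, two-sided alpha 0.05, power 85%, 200 per group, total 800.

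n = 2 × (z₀.₉₇₅ + z₀.₈₅)² × (SD/difference)² = 2 × (1.960 + 1.036)² × (0.7/0.2)² ≈ 220 per group.

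The stated 200 does not reproduce; it gives 81.5% power. That is a separate matter. The Results section gives 400 per arm (200 per arm in each of the urban and rural settings), so the overall comparison uses 400.

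**3. Cost of a binary version, if one were used**

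The documents give no mean, SD, distribution or cut-off for the CSQ-8. Two assumptions are therefore needed: the score is roughly normal, and the standardized planning effect d = 0.2/0.7 = 0.286, stated for knowledge, attitude and behavior, also applies to satisfaction.

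Information kept by a cut at proportion p: E = φ(z_p)² / [p(1 − p)].

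Power at 400 per arm: Φ(d × √(400/2) × √E − 1.96) = Φ(4.041 × √E − 1.96).

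| Analysis | E | Information lost | Effective n of 400 | Power |
|---|---|---|---|---|
| Score as continuous | 1 | 0 | 400 | 98% |
| Median cut | 0.637 | 36% | 255 | 90% |
| 70/30 | 0.576 | 42% | 230 | 87% |
| 80/20 | 0.490 | 51% | 196 | 81% |
| 90/10 | 0.342 | 66% | 137 | 66% |

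Example, median cut: E = 0.399²/0.25 = 0.637, and Φ(4.041 × 0.798 − 1.96) = Φ(1.26) = 0.90.

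A direct two-proportion calculation at 400 per arm gives 89% at the median cut. For uneven cuts the result depends on the side on which most controls fall: 84% or 76% at 80/20, and 71% or 58% at 90/10. The tabulated values lie between these.

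**4. Sensitivity to the shape of the score**

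For an assumed total of 8 to 32 with a ceiling (latent normal, SD 4, best possible cut), the loss is 35% with 8% of scores at the maximum, 32% with 19%, 26% with 35%, 13% with 55% and about zero with 73%. For a logistic-shaped score a median cut loses 18%.

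**The case against.** A journal article condenses a fuller plan, and a responder cut-off is the kind of detail left to that plan. This stands: the absent cut-off is not itself a fault. It does not explain the paragraph, which assigns contradictory ranks and methods to a named outcome. Added detail elsewhere would not make those statements agree.

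A reader might infer that the plan throws away a third or more of the information on satisfaction. The documents do not support that. It would require that the score is in fact dichotomised and that it is roughly normal, and neither is stated. Under a marked ceiling or heavier tails the loss is smaller, and a linear analysis of the score would incur none. Power figures at 200 per arm would also mislead, since 200 is the number in one setting. At 400 per arm even a median cut would exceed the planned 85%, if the borrowed effect held.

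A reader might also infer that the adjusted analysis drops the subject random effect and so gives wrong standard errors. The closing sentence is too ambiguous for that. Adding covariates to the model could mean the mixed model just described, and the linear regression could be meant for other outcomes. What can be said is that a linear regression is not the covariate-adjusted form of a logit model.

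Finally, satisfaction does not drive the sample size, and the wording about changes is an expectation in the abstract, not a specified estimand. The Discussion already expects higher satisfaction in the intervention group. Both remarks are fair, and the wording point is minor. Still, satisfaction is named as primary, so its rank matters.

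**Conclusion.** The contradiction is real and rests on the text alone: one outcome, two ranks, and four named methods that imply three data types. Log-rank and Cox have no defined event to work on, and the binary label does not match the instrument as described. The attachment of the linear-regression sentence to satisfaction is likely from its position but not certain.

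The statistical cost is conditional. For a roughly normal score that is dichotomised, it is about 36% of the information at the most favourable cut and up to 66% at 90/10. With the planning effect borrowed from knowledge, attitude and behavior, power at 400 per arm would go from about 98% to between 90% and 66%. These figures show what is at stake in the choice of form; they are not a property of the plan as written.

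**What to change.** - Give satisfaction one rank. Secondary agrees best with the Outcomes and Sample Size Justification sections.
- Remove the log-rank test and Cox model for this outcome.
- Analyse the CSQ-8 total score with a linear mixed model: group, visit, group-by-visit and setting as fixed effects, subject as random effect. Report the between-group difference at month 6 with its confidence interval.
- Use the same model with covariates for the adjusted analysis, and say which outcomes the linear-regression sentence covers.
- If a binary version is kept, make it supportive, with a prespecified cut-off and a logistic mixed model for both the unadjusted and the adjusted analysis. Making the binary form the main one in the same consistent way would also remove the contradiction, at the possible loss of precision shown above.
- Describe the result as a difference between groups at follow-up, not as a change.

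The cost is a revision of wording in the protocol and analysis plan, with no new data. The revision should be dated and made before follow-up satisfaction is compared by group; if that comparison has already been made, the report should say so.

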### Sample Size Justification

The sample size calculation was based on knowledge, attitude, and behavior outcomes, as reported in previous studies [22]. To detect a mean change of 0.2 with an SD of 0.7 at a 2-sided .05 α level of significance and a power of 85%, a sample size of 200 individuals in each group is needed. The total participant sample size will be 800.

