## Results

Data collection was conducted between the period of June and December 2018. The collection of baseline data from 800 study participants in both the intervention (n=400) and control groups (n=400), which were stratified by urban (control group: n=200; intervention group: n=200) and rural settings (control group: n=200; intervention group n=200), has been completed. Follow-up data collection for months 3 and 6 is ongoing. We expect the follow-up data collection to be completed by October 2019. We are currently analyzing the baseline data and generating reports, which will be presented in our upcoming manuscript.

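### The adjusted satisfaction analysis names a linear regression, which conflicts with the logit mixed model and its random subject effect; pooling both follow-up visits without that effect would raise the type I error above 5%

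*Protocol article*

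**What the plan says.** The Statistical Analysis section treats satisfaction as a binary secondary objective, modelled by a mixed model with binomial distribution and logit link. Group is the fixed effect, and "subject data will be used as random effects". Confounders that differ between groups at the .20 level are then handled as follows: "covariates will be added to the model, and a linear regression model will be used". Earlier in the same section, satisfaction is also listed among the primary outcomes, for a log-rank test and a Cox model.

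On timing, the Study Groups section says "Follow-up visits were conducted at 3 and 6 months from the baseline in both groups" and "Follow-up data were gathered on anthropometric measurements, diabetes KAPs, blood sugar testing, and satisfaction with medical care". Satisfaction is not in that section's list of baseline data. The sections on outcomes and on the CSQ-8 do not assign satisfaction to a particular visit. The article states no within-person correlation.

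**The concern.** A logit mixed model and a linear regression differ in two ways that matter here. The first is the scale: log odds for a binary outcome against a mean difference for a score. The second is the error structure: the mixed model has a subject term that links values from the same person, while a linear regression, as usually understood, has independent errors and no such term.

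If an analyst follows the second half of the sentence and has two satisfaction values per person, the step from unadjusted to adjusted analysis drops the only stated device for repeated values. Group does not change within a person. Positive correlation between visits would therefore make the reported standard error of the group effect too small, the interval too narrow and a false claim of a group difference too likely. The Discussion anticipates higher satisfaction in the intervention group, so this result will be looked at. The unadjusted and adjusted estimates would also be on different scales and could not be compared directly.

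**Working it through.** **The sentence itself.** The first half adds covariates to the model, and the model just described is the mixed model. That keeps the logit link and the subject effect. The second half names a linear regression, which is not a binomial logit model and has no subject term. Both cannot describe one analysis.

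**Inputs for the size.**
- 400 participants per arm (Results).
- Follow-up visits at months 3 and 6 (Study Groups).
- Two-sided 0.05. This is given in Sample Size Justification and is assumed here to apply to the satisfaction test.
- Within-person correlation ρ between the two visits: not in the article; assumed 0.3, 0.5 and 0.7.
- Also assumed: equal variance σ² at both visits, both values present for everyone, ρ not negative.

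**The plan's own figures.** The one that matters here is the nominal 5%, which the formula below returns at ρ = 0. The sample size plays no part, because the inflation does not depend on n. For completeness, a difference of 0.2 with SD 0.7 at 85% power needs 2 × (1.960 + 1.036)² × 0.7² / 0.2² = 220 per group, against the stated 200. That is a separate matter.

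**Variance of the group difference, n per arm, two values per person.**
- Reported by a pooled linear regression, with 2n records per arm taken as independent: 2σ²/(2n) = σ²/n.
- True: each person's mean has variance σ²(1 + ρ)/2, so the difference between arms has variance 2 × σ²(1 + ρ)/(2n) = σ²(1 + ρ)/n.
- Ratio of true to reported: 1 + ρ.

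With n = 400 the reported standard error is σ/√400 = 0.050σ. At ρ = 0.5 the true one is 0.050σ × √1.5 = 0.061σ.

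**Type I error** = 2 × [1 − Φ(1.96/√(1 + ρ))]:

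| ρ (assumed) | Reported SE / true SE | Type I error | Coverage of nominal 95% interval |
|---|---|---|---|
| 0 | 1.000 | 5.0% | 95.0% |
| 0.1 | 0.953 | 6.2% | 93.8% |
| 0.3 | 0.877 | 8.6% | 91.4% |
| 0.5 | 0.816 | 11.0% | 89.0% |
| 0.7 | 0.767 | 13.3% | 86.7% |
| 1 | 0.707 | 16.6% | 83.4% |

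A simulation of 10,000 trials per value, 400 per arm and two stacked visits, gave 8.5%, 10.7% and 13.0% at ρ = 0.3, 0.5 and 0.7. The same simulated trials analysed with one visit per person gave 4.6% to 5.2%, which is the nominal level within simulation error.

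**The case against.** A reader might infer that the plan has dropped the subject effect and that its adjusted satisfaction test runs at 9% to 13%. The article does not support that, for three reasons.

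- **The subject effect is not said to be dropped.** The first half of the sentence, taken plainly, keeps it. Nothing in the text says that the regression is ordinary least squares or that errors are taken as independent.
- **Two satisfaction values per person are not established.** The list of follow-up data does not assign items to visits. It includes blood sugar testing, which the Blood Sugar Testing section places only at baseline and 6 months, so it cannot mean every item at every visit.
- **Nothing says both visits are stacked in the regression.** If the linear regression really is a separate model, one record per person is just as open, and there is then no inflation.

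All three stand, and they make the type I error figures conditional. They do not remove the conflict. A random subject effect with a single binary value per person has nothing to be estimated from, so the stated mixed model presupposes repeated values, and months 3 and 6 are the only follow-up visits named. The section also follows the same pattern for the primary outcomes, where a log-rank test is followed by a different named model, Cox, for adjustment. That makes a change of model a natural reading here too.

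It may also be said that if satisfaction is confirmed as binary, the linear regression falls away and the issue with it. That is so only if the clause is then removed. If satisfaction is instead settled as a CSQ-8 score, linear regression looks suitable and the missing subject term remains.

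Finally, a condensed article may leave the handling of visits to the full plan. That excuses silence on detail, but not a sentence that names two incompatible models.

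**Conclusion.** The point holds as a contradiction in stated text with a conditional consequence. The adjusted step for satisfaction names a model that does not match the one to which it adds covariates. Under either reading, the linear regression clause is wrong or inconsistent.

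The consequence has a size only if the regression is fitted to both visits without a subject term or clustered variance. On the assumptions listed, the type I error is then 8.6%, 11.0% or 13.3% at ρ = 0.3, 0.5 or 0.7, within a possible range of 5% to 16.6%. The standard error is 12%, 18% or 23% too small. If one visit is analysed, or the subject effect is kept, the level stays at about 5%. These figures show what the wording allows; they do not measure what the trial will do.

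**What to change.** Delete the clause that names a linear regression. State that the covariates are added to the same binomial logit mixed model, that the random subject effect is kept, and which follow-up visits enter.

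Two alternatives are acceptable if stated in advance, but they estimate something different from the mixed model and are not interchangeable with it:
- analyse month 6 alone, with one record per person; or
- fit the regression to both visits with standard errors clustered by subject.

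If satisfaction is to be analysed as a CSQ-8 score, use the linear counterpart for both the unadjusted and the adjusted model, with the subject term in each.

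The cost is one sentence and no new data. The only downside is a wider adjusted interval than a pooled regression would report: by √1.3 = 1.14, √1.5 = 1.22 or √1.7 = 1.30 times on the same scale for ρ = 0.3, 0.5 or 0.7. That is the correct width.

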## Results

Data collection was conducted between the period of June and December 2018. The collection of baseline data from 800 study participants in both the intervention (n=400) and control groups (n=400), which were stratified by urban (control group: n=200; intervention group: n=200) and rural settings (control group: n=200; intervention group n=200), has been completed. Follow-up data collection for months 3 and 6 is ongoing. We expect the follow-up data collection to be completed by October 2019. We are currently analyzing the baseline data and generating reports, which will be presented in our upcoming manuscript.

## Discussion

We anticipate that our results will show a significant difference in nutrition KAPs between the study groups. The study participants receiving tailored dietary education will likely show better improvements in their KAPs and overall diabetes management. We also anticipate that satisfaction with care (measured by the CSQ-8) will be higher in the intervention group, owing to the unique features of our interactive, telephone-linked, personalized, human-centered decision support system (eg, personalized dietary education and reminder alerts for completing the food log). We also expect to see urban-rural differences across the intervention and control groups. Our dietary decision support system is the first of its kind to be successfully implemented in a lower-middle–income country such as India, and it has the potential to inform dietary data management on a wider scope. Key gaps in diet-related interventions are centered on the tailoring, sustainability, and evaluation of such interventions [15,23]. Studies that were conducted to examine the effectiveness of existing diet apps highlighted the need for tailoring approaches that can address the personal needs of the users [23]. Another crucial gap in the design approaches of existing diet apps is the challenge of identifying which specific components are associated with intervention effectiveness. The task of identifying specific components associated with effectiveness becomes an arduous one when human-centered approaches are not effectively incorporated into the design process. A systematic review investigating the effectiveness of eHealth and mobile health interventions that promote physical activity and healthy diets across 13 low- and middle-income countries showed that it was not possible to identify the specific components associated with app effectiveness among the included studies [23]. A human-centered design approach is needed to address these challenges. The uniqueness of our nutrient data capture process is demonstrated by its incorporation of human-centered, cultural, and contextually relevant features—diet capture in both English and Hindi, diet conversion into caloric components, sustained diet data collection and participant adherence through telephone-linked care, and auto-generated reminders. We conducted focus groups with the study population in addition to literature reviews, with the aim of identifying user characteristics, needs, and preferences that potentially influence users’ satisfaction with and use of the interactive, telephone-linked, personalized, human-centered decision support system [24-26].
